We will use generalized linear models to assess the effects of the intervention on the key study outcomes. We anticipate that most will use the Gaussian family of distributions with the log link function, yet some are likely to be severely skewed or demonstrate a better fit using the Poisson family or nonparametric regression models. Estimated mean differences in the post-intervention values controlling for the baseline assessments will be generated from each respective outcome model. These estimated adjusted mean differences will be used to evaluate the effect of the study group and to serve as measures of effect sizes. For example, if the Sit Less group sits for 60 minutes less than the control group after the intervention, this is crucial to comprehending the effects of the intervention and to inform the design of future large-scale RCTs. Furthermore, we will generate bootstrapped 95% confidence intervals around each adjusted mean difference. All models and estimations of adjusted mean differences will use the robust or sandwich estimator of variance. While we will consider results statistically significant if p < 0.05, we will not adjust this critical alpha level for the multiple outcomes assessed in this work, as the focus is on the estimated mean differences for informing future work.

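### A Gaussian model with a log link is a poorly matched default for a baseline-adjusted mean difference in natural units; an identity link is at least as precise and protected by randomisation

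*Protocol article*

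**What the plan says.** Section 2.13 of the protocol article chooses generalized linear models for the effects on the key outcomes and names the expected default: "We anticipate that most will use the Gaussian family of distributions with the log link function". The same sentence allows exceptions: "some are likely to be severely skewed or demonstrate a better fit using the Poisson family or nonparametric regression models".

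The effect measure follows: "Estimated mean differences in the post-intervention values controlling for the baseline assessments will be generated from each respective outcome model". The worked example is an absolute difference, "if the Sit Less group sits for 60 minutes less than the control group after the intervention", and the differences are meant to inform the design of later large trials. For inference, "we will generate bootstrapped 95% confidence intervals around each adjusted mean difference" and "All models and estimations of adjusted mean differences will use the robust or sandwich estimator of variance".

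No reason is given for the log link. The article does not say whether the baseline covariate enters raw or logged.

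**The concern.** The coefficient of a log-link model is a log ratio of means. With an untransformed baseline covariate, the model also makes the follow-up value grow exponentially with baseline, although a measure taken twice on the same person is usually related to itself more nearly linearly. A difference in minutes is obtained only by averaging predictions over the sample.

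Whether that average can be trusted when the curve is wrong depends on the link. With a canonical link, the estimating equations force the mean prediction in each arm to equal the observed arm mean, so randomisation protects the averaged difference. The identity link is canonical for the Gaussian family and the log link for the Poisson. Gaussian with log is neither.

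At stake are the precision and calibration of the estimates that this pilot will pass on to the next trial, from at most 35 people per arm and fewer after non-completers are left out.

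**Working it through.** **Plan's own figures.** The article gives no SD, correlation or distribution for any outcome, so it has no figure on this point to reproduce. Its only sample-size calculation concerns feasibility: ln(1 − 0.95)/ln(1 − 0.10) = 28.4, so 29, close to the stated 30. It has no bearing on the outcome model.

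**Why the link matters.** Write μ for the fitted mean and x for the covariates (intercept, arm, baseline). The fits solve:
- Gaussian, identity: Σ(y − μ)x = 0
- Poisson, log: Σ(y − μ)x = 0
- Gaussian, log: Σμ(y − μ)x = 0

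In the first two, residuals sum to zero within each arm. In the third, only residuals weighted by the fitted mean do. High fitted values, where a right-skewed outcome is most variable, therefore get extra weight. A sandwich or bootstrap interval describes the spread around whatever value this fit converges to; it does not move that value.

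**Inputs from the article.**
- 35 per arm (section 2.2).
- Sedentary time of 10 to 11 hours a day (Introduction); midpoint 10.5 × 60 = 630 min.
- Half of it in bouts over 30 minutes (Introduction); 0.5 × 630 = 315 min.
- Effect of −60 min, from the example in section 2.13.

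**Assumed inputs.** Total sitting is normal with SD 100. Prolonged sitting is gamma with SD 100, 130 or 180, so CV = SD/315 = 0.32, 0.41 or 0.57. Baseline correlation is 0.65 and baseline enters untransformed. The true effect is either additive (−60 for everyone) or proportional (−60/315 = −19%).

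**Simulation.** Each of 4,000 trials of 70 was fitted by identity-link ANCOVA and by the log-link Gaussian model with averaged predictions. The variance ratio is log over identity.

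| Outcome, true effect | Identity, mean | Log link, mean | Variance ratio |
|---|---|---|---|
| Total sitting, additive | −60.0 | −59.4 | 0.99 |
| Prolonged, CV 0.32, additive | −59.5 | −57.5 | 1.12 |
| Prolonged, CV 0.41, additive | −59.7 | −56.6 | 1.16 |
| Prolonged, CV 0.57, additive | −60.0 | −55.2 | 1.34 |
| Prolonged, CV 0.32, proportional | −59.8 | −60.3 | 1.11 |
| Prolonged, CV 0.41, proportional | −59.8 | −60.6 | 1.17 |
| Prolonged, CV 0.57, proportional | −59.9 | −61.5 | 1.32 |

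Attenuation in the additive rows is (60 − 57.5)/60 = 4% to (60 − 55.2)/60 = 8%. With 20,000 participants per simulated trial, the additive log-link means are −57.3, −56.0 and −53.9 (identity −59.9 to −60.4). The shortfall is up to (60 − 53.9)/60 = 10%, so this is misspecification and not small-sample noise. Repeated runs at these settings, small and large, span about 1.09 to 1.35 for variance and 4 to 11% for attenuation.

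**In sample-size terms.** A ratio of 1.1 leaves 35/1.1 = 31.8 effective participants per arm; 1.35 leaves 35/1.35 = 25.9.

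**Sensitivity.** At CV 0.57 with correlation 0.7 the gamma ratios are 1.39 to 1.45. A heavier lognormal tail at that CV and correlation gives 1.64 to 1.86. In that lognormal case with an additive effect, a logged baseline worsens the attenuation from −54.3 to −51.0. The Poisson model with log link, which the plan allows, stayed within about 1 minute of −60 in the gamma runs, with variance 1.03 to 1.10 times identity.

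**The case against.** A reader might infer that a log link contradicts the stated effect measure. It does not. Section 2.13 says the differences are generated from each fitted model, and averaging predicted means from a log-link model gives a difference in minutes. The mismatch is one of native scale and robustness.

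The best defence is that the sentence setting the default also provides for outcomes that misbehave: severely skewed ones may go to Poisson or nonparametric regression. This stands in part. It removes the worst cases, such as the lognormal ratios above, from the fair size of the problem. It does not cover moderate skew, where the loss already appears at a CV near 0.3 and an analyst could reasonably stay with the default.

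It also stands that every SD, shape and correlation used here is assumed, that attenuation needs an additive effect, and that total sedentary time is unaffected.

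A reader might also treat the missing rule for leaving the default as a defect. Such detail commonly sits in a statistical analysis plan, which is not shown, so naming the outcomes in advance is offered here only as a preference.

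**Conclusion.** The point holds as a poorly matched default, not as an error in the estimand. For outcomes with moderate right skew left on the Gaussian model, the log link costs about 10 to 35% in variance. It pulls an additive effect towards zero by about 4 to 11%; under a proportional effect there is no attenuation, only the variance cost. For near-normal total sedentary time there is no material difference. It would be wrong to conclude that the plan attenuates effects on skewed outcomes in general.

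The figures rest on assumed distributions (CV about 0.3 to 0.6, correlation about 0.65), full follow-up of 35 per arm and an untransformed baseline. The lack of protection by randomisation rests on none of these. In the scenarios tested, the identity link stayed close to the true difference and lost nothing material. Severity is low to moderate: section 2.2 disclaims a powered hypothesis test, and section 2.13 puts the weight on estimation.

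**What to change.** - In section 2.13, make the Gaussian family with **identity** link the default for continuous outcomes kept on the Gaussian model, including prolonged sedentary time: post-intervention value on arm plus baseline value. The arm coefficient is then the adjusted mean difference. Keep the planned robust standard errors and bootstrap intervals.
- Keep the Poisson family for counts and severely skewed outcomes, and state that the mean difference is obtained by averaging predictions under each arm. Preferably list these outcomes before the data are seen, rather than choosing by observed fit.
- Do not require log-transformed analyses for outcomes that can be zero, such as the percentage of time above the glucose range.

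The cost is one word in the model statement, one sentence on averaging and a short list of outcomes. No data collection changes, and nothing material is lost for total sedentary time.

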### 2.2. Participants and sample size

We will recruit 70 patients with CVD who 1) are 18 years or older, 2) have at least one of the following conditions: history of heart attack, coronary/carotid artery disease, ischemic heart disease, peripheral artery disease, a stent placed in the heart or leg or had a coronary artery bypass surgery, 3) self-report of sitting ≥ 8 hours/day, 4) ability to stand and walk, and 5) ownership of a smartphone. We will exclude those who are 1) using an activity tracker, 2) currently participating in exercise or cardiac rehabilitation programs, 3) non-English speaking, 4) classified as unstable (e.g. heart failure, uncontrolled arrhythmia), have kidney disease that limits daily water intake, or any conditions that prevent standing or walking due to physical or cognitive limitations, such as cognitive impairment, severe pain, problems with lower limbs, or a history of surgeries that limit movement, and 5) currently pregnant.

As a pilot/feasibility study, we do not propose a fully powered, hypothesis-testing trial. The primary outcome of this study is the feasibility and acceptability of the Sit Less program, which is not dependent on effect sizes. Therefore, we did not calculate the sample size based on the effect sizes but based on the calculation to identify potential problems in feasibility/acceptability. According to Viechtbauer et al. [28], if the feasibility issue occurs with a 10% chance, a sample size of 30 is required to identify the feasibility issue with a confidence of 95%. The total sample of 70 (35 in the intervention group and 35 in the control group) was estimated to allow sufficient piloting of study protocols and examination of the feasibility of intervention activities and measures to inform future research.

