### 2.10. Secondary outcomes

#### 2.10.1. Physical activity

Time spent standing and walking (stepping), number of sitting-to-standing transitions, and number of step counts will be measured using the activPAL 3 device. The activPAL 3 has demonstrated greater criterion validity compared to video observation for measuring physical activity [46].

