## Discussion

The study aims to evaluate a multi-technology-based and individually tailored intervention to reduce sedentary behavior in CVD patients. The primary outcomes are the feasibility, acceptability, and primary efficacy in changing sedentary behavior (change in total minutes spent in sedentary behavior, change in prolonged sedentary time, and number of sit-to-stand transitions) measured by the activPAL. Secondary outcomes are changes in physical activity measured by the activPAL and changes in cardiometabolic biomarkers measured by CGM and dried blood spot cards, along with changes in psychosocial constructs.

Despite the important role of sedentary behavior in cardiac outcomes in CVD patients, there are few studies focusing on reducing sedentary behavior in this understudied population. In this study, we will test a sedentary behavior reduction intervention program based on habit theory that leverages wearable technology, for CVD patients. The proposed sedentary behavior reduction program is innovative because it side-steps barriers of exercise (e.g., fear of heart discomfort, fatigue) in CVD patients and focuses on breaking sedentary time with short bouts of standing and walking, which can be easily implemented in the natural environment. Other novel aspects of this study include using multiple technologies, including a Fitbit and a smart water bottle to motivate participants to stand up, and the development of an automatic, yet tailored text message algorithm. The study will also employ a validated measure for sedentary behavior (i.e., activPAL) and sensitive biological indicators linked to sedentary behavior, such as 24-hour glucose monitoring parameters.

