However, there are also several limitations and concerns. First, our ultimate goal is to disrupt prolonged sedentary behavior by encouraging movement every 30 minutes. However, there’s a limitation with the Fitbit device as it only sends alerts after one hour of inactivity. To address this issue, we will send text messages and provide tips that assist participants in gradually transitioning from breaking sedentary behavior every hour to every 30 minutes. Once they have successfully established the new habit with the aid of their Fitbit’s one hour alert, we will then motivate them to progress towards breaking their sedentary behavior every 30 minutes. Another concern is the risk of cross-contamination between different arms of the study, a result of enrolling subjects from a single hospital. The applicability of the findings may also be limited when considering a wider demographic, such as urban populations with access to extensive public transportation systems. Lastly, this study does not address other lifestyle factors tied to CVD management, such as dietary habits. However, the primary focus is to establish the efficacy of this intervention in reducing sedentary behavior before addressing other lifestyle factors.

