## Conclusions

Though people with CVD are particularly prone to high levels of sedentary behavior and prolonged sedentary behavior, there are few interventions targeting sedentary behavior in people with CVD. Implementing frequent but short periods of sedentary breaks (standing or walking) in daily life can be attainable behavioral goals that can reduce total sedentary time and yield substantive health improvements in people with CVD. In our pilot randomized control trial, we will develop a multi-technology-based intervention to decrease sedentary behavior among CVD patients. This intervention will utilize a Fitbit device with sedentary break reminders, a smart water bottle, and personalized weekly text messages for a sample of 70 individuals with CVD. The study will determine if a low-touch, home-based mHealth intervention is feasible, acceptable, and effective for CVD patients in decreasing their sedentary behavior. The results could guide the development and implementation of future studies targeting sedentary behavior in a broader population, ultimately contributing to the prevention of CVD complications and the enhancement of cardiometabolic health.

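### Section 2.2 makes feasibility and acceptability the primary outcome, yet four unranked sedentary measures are also primary, are tested at unadjusted p<0.05, and are tied to a promise to determine effectiveness

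*Protocol article*

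**What the plan says.** Section 2.2 is explicit about the kind of trial this is: "As a pilot/feasibility study, we do not propose a fully powered, hypothesis-testing trial". It continues: "The primary outcome of this study is the feasibility and acceptability of the Sit Less program". The sample size comes from the chance of seeing a feasibility problem at least once, and the section says that effect sizes were not used.

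Other parts read differently:

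- Section 2.9 is headed as primary outcomes. Besides feasibility and acceptability (2.9.1), it contains sedentary behavior (2.9.2): total daily time, prolonged time at two cut-offs (over 30 and over 60 minutes), and sit-to-stand transitions. No order among them is given.
- The Discussion confirms this: "The primary outcomes are the feasibility, acceptability, and primary efficacy in changing sedentary behavior".
- Section 2.10.1, under secondary outcomes, includes "number of sitting-to-standing transitions".
- Section 2.13 sets the decision rule: "While we will consider results statistically significant if p < 0.05, we will not adjust this critical alpha level for the multiple outcomes assessed". The same sentence gives the reason, which is that the focus lies on estimated mean differences to inform later work. Bootstrapped 95% confidence intervals are planned around each adjusted difference.
- The Introduction gives the aim as feasibility, acceptability and preliminary efficacy. The Abstract and Discussion speak of primary efficacy instead.
- The Conclusions go furthest: "The study will determine if a low-touch, home-based mHealth intervention is feasible, acceptable, and effective for CVD patients".

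**The concern.** The article gives two answers to which outcome is primary, and the two call for different inference. If feasibility and acceptability are primary, the sedentary measures are exploratory: estimates with intervals are enough and no multiplicity control is needed. If sedentary behavior is also primary, the reader expects one named measure (or a rule for several), a power basis and control of the error rate. The article labels the measures as in the second case and treats them as in the first.

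What is at stake is the trial's headline. With four co-equal primary measures, a significance threshold applied to each, and a stated intention to determine effectiveness, a single chance p<0.05 could be reported as a positive primary result. The conflict also leaves open, after the data are in, which definition of primary to report, and whether a result on transitions counts as primary or secondary.

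**Working it through.** **1. The plan's own sample-size figure.** Inputs from 2.2: problem probability 0.10, confidence 95%, stated n = 30. The number needed to see the problem at least once is n = ln(1 − 0.95)/ln(1 − 0.10) = ln 0.05/ln 0.90 = 28.43, rounded up to 29. With n = 30 the chance is 1 − 0.90^30 = 95.8%; with the 35 per arm planned it is 1 − 0.90^35 = 97.5%. The stated figure is therefore sound for its purpose. It contains no between-group difference, SD or alpha, so it says nothing about the sedentary comparisons.

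**2. The statements side by side.**

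| Place | Primary outcome | Efficacy claim |
|---|---|---|
| Introduction (aim) | not specified | preliminary |
| 2.2 | feasibility and acceptability | none; not a fully powered hypothesis-testing trial |
| 2.9 | feasibility, acceptability, sedentary behavior | none stated |
| Discussion, first paragraph | feasibility, acceptability, sedentary behavior | primary efficacy |
| Conclusions | not specified | will determine whether effective |

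**3. Number of primary efficacy measures.** From 2.9.2: total time (1), prolonged time at two cut-offs (2) and transitions (1), which makes 4. Counting prolonged time once gives 3.

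**4. Chance of at least one false positive.** Assume no true effect and two-sided tests at 0.05 (sidedness is not stated).

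- Independent tests: 1 − 0.95^4 = 1 − 0.8145 = 18.5%.
- Equally correlated normal test statistics with correlation ρ and c = 1.96: 1 − ∫ φ(z)[Φ((c − √ρ z)/√(1 − ρ)) − Φ((−c − √ρ z)/√(1 − ρ))]^4 dz. This gives 15.6% at ρ = 0.5 and 13.0% at ρ = 0.7.
- With three measures: 1 − 0.95^3 = 14.3% if independent.

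The documents give no correlations, so ρ is assumed. These are two-sided figures. Counting only chance results that favor the program, independence gives 1 − 0.975^4 = 9.6%, against 2.5% for a single measure.

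**5. What can be said about power.** The documents give no SD. With 35 per arm, 80% power at two-sided 0.05 needs a standardized difference of (1.96 + 0.84) × √(2/35) = 0.67. For the 60-minute example in 2.13, power would be 88%, 71%, 55% or 39% if the residual SD were 80, 100, 120 or 150 minutes (assumed values). Whether power is adequate therefore cannot be read from the article, only that it was not calculated.

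**The case against.** The best defense is that this is openly a pilot. Not adjusting alpha is disclosed and justified by a focus on estimation, differences with confidence intervals are already planned, and the stated aim is only preliminary efficacy. The feasibility and acceptability decisions rest on predefined percentages (2.9.1), which no p-value can change. Disclaiming a fully powered hypothesis-testing trial does not forbid reporting p-values, and the phrase about primary efficacy may be a slip for preliminary. All of this stands, and it means that the unadjusted level alone is not an error. It does not reconcile 2.2 with 2.9 and the Discussion, place transitions in one tier, or square the Conclusions with the aim.

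Four stronger readings are tempting but not supported:

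- *The sedentary comparisons lack power.* The article shows only that no power calculation was made, and it says so itself.
- *Every listed secondary measure will be tested, so false positives are nearly certain.* Section 2.13 models the key study outcomes, a set it does not list. Many measures are strongly linked: time below, in and above glucose range sum to 100%. Any overall figure would rest on a reader's own count and on independence.
- *The next trial will be sized on the pilot's point estimate.* Section 2.13 says that the adjusted differences will serve as effect sizes and inform later design. It gives no sizing rule and does not select on significance.
- *The Discussion promises to establish efficacy.* The words "the primary focus is to establish the efficacy of this intervention in reducing sedentary behavior" stand among the limitations and explain why diet and other lifestyle factors come later. They are loosely worded but are not a decision rule; the clear overclaim is in the Conclusions.

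**Conclusion.** The point holds as an internal contradiction with a practical consequence. The article gives two definitions of the primary outcome, puts one measure in two tiers, and joins an unadjusted significance rule to a statement that effectiveness will be determined, on a sample size that was not built for that question. If the program had no effect, the chance of at least one nominally significant primary efficacy measure would be about 13% to 18.5%, assuming four two-sided tests with a common correlation between 0.7 and 0. Roughly half of such results would point in the program's favor.

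This should be fixed, but it does not undermine the design: the feasibility and acceptability conclusions are unaffected. It is also not a matter that can be left to an analysis plan, because the conflicting statements about what is primary and what will be concluded are in the article itself.

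**What to change.** - State in the Abstract, 2.2, 2.9 and the Discussion that feasibility and acceptability are the sole primary outcome.
- Name one key preliminary-efficacy measure, for example total daily sedentary time, and make the other sedentary measures secondary. List transitions once, in either the sedentary or the physical activity section.
- In 2.13, base conclusions on the adjusted differences with their 95% confidence intervals. Either drop the p<0.05 rule or say that it supports no claim of efficacy.
- Use preliminary-efficacy wording in place of primary efficacy (Abstract, Discussion), the establishing of efficacy (Discussion, limitations) and effective (Conclusions).

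Another consistent repair would keep sedentary behavior primary, with one named measure, its own power calculation and control of alpha. That is a larger change and fits the pilot aim less well.

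The recommended repair costs only wording, plus the IRB approval and registry update that 2.15.1 requires for amendments. It adds no participants, measurements or changes to the intervention. What is given up is a claim of effectiveness that this sample was not sized to support. It should be settled before any outcome is analyzed by arm.
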